#### *2.6.5 Procedure for unblinding if needed*

Situations in which the study team may need to break the blind may include an allergic reaction to the study drug or a psychological response to the drug that, in the investigator's opinion, requires unblinding to properly assess. The decision to unblind the study staff will be determined by the clinician present at drug visits if unblinding must occur outside of a study visit for any reason.

There are two unblinded individuals who have access to the randomization assignment, chosen at the beginning of the study and not involved in data collection. In the event the research staff must be unblinded, the contact information for both individuals (phone, email) is available to all blinded research staff. Study staff will communicate the study ID and the unblinded staff will respond with the complete randomization assignment for that participant, all three drug visits.

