## **2.5 Interventions**

### *2.5.1 Intervention description*

After baseline visit, each participant will receive placebo, 80mg MDMA HCl, and 120mg MDMA HCl in a randomized order. Given the within-subjects design of the study, each participant will receive all three of the specified doses across the duration of the trial. Drug visits will be scheduled 10-14 days apart to avoid drug carry-over effects. Participants will arrive fasted for drug visits in the morning to reduce the risk of emesis. They will complete a urine drug screen and pregnancy test (if applicable) and have their baseline vitals recorded at the Stanford Center for Cognitive and Neurobiological Imaging, where they will be met by the study clinician. Participants will be instructed to orally ingest pills with water or an electrolyte solution. For safety reasons, pulse, blood pressure, temperature, and oxygen saturation will be monitored and recorded every 30 minutes throughout the drug visit. The total visit time for drug visits will be 6-8 hours.

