### *2.6.3 Implementation*

Unblinded study personnel are responsible for generating the random dose assignments. None of the blinded study staff had access to the subject ID dose assignments at any point in the randomization process. Participants are considered to be enrolled in the study once they have finished the in-person screening visit and met all the criteria. After successful enrollment, the participant is assigned a study ID, with the first participant enrolled assigned 001, the second 002 and so on. MDMA and placebo pills were obtained from the Multidisciplinary Association for Psychedelic Studies (MAPS). Before a study visit

involving drug administration, the unblinded study personnel will reference the subject ID and the visit number on the randomization assignment document to make the dose determination. For example, if subject 001 is scheduled for their second drug visit, the unblinded personnel would reference the randomization assignment document for 001, look for their assigned dose for the second drug visit, and count pills according to the information on the assignment. The drug will be delivered to the blinded research team with a label stating the subject ID and visit number.

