#### *2.6.4 Blinded personnel*

The study design is double blind, both the participant and the research team, including study clinicians, are blinded to the dose assignment. Blinded research staff includes clinical research coordinators, study clinicians, research nurses, and scanning personnel. All data collection is conducted by the blinded research team. Data analysts for both the interim analysis and the final analysis are unblinded.

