#### Allergic Reaction

- Research visit will be discontinued.
- In case of mild to moderate allergic reaction, diphenhydramine 25mg PO will be administered by the clinician. Mild symptoms could include though are not limited to hives/rashes and itching.
- If symptoms are severe, including but not limited to swelling of the throat/and or tongue, difficulty breathing or swallowing, and/or drop in blood pressure, administer EpiPen 0.3mg Auto-injector, preferably by the clinician. 911 should be called simultaneously by a clinical research coordinator.
- For oxygen saturation <85%, a nasal cannula will be placed by the clinician until saturation reaches at least 90%.

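### Breaking the blind releases all three visits' doses, so staff can learn doses not yet given; release by visit would limit this

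*Protocol*

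**What the plan says.** Section 2.6.5 of the protocol sets out how the code is broken. The request carries no visit number: "Study staff will communicate the study ID", and in reply "the unblinded staff will respond with the complete randomization assignment for that participant, all three drug visits". The situations it gives as examples are "an allergic reaction to the study drug or a psychological response to the drug that, in the investigator's opinion, requires unblinding to properly assess".

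Section 2.5.1 fixes the within-subject structure: "each participant will receive placebo, 80mg MDMA HCl, and 120mg MDMA HCl in a randomized order". Section 2.6.4 says that "both the participant and the research team, including study clinicians, are blinded to the dose assignment", and adds: "All data collection is conducted by the blinded research team".

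Section 2.6.3 shows how the list is used for dispensing: "the unblinded study personnel will reference the subject ID and the visit number on the randomization assignment document". The list can therefore already be read one visit at a time.

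On what follows a reaction, the Allergic Reaction part of section 2.7 says only: "Research visit will be discontinued". Section 2.11.6 allows a reduced form of participation for those who stop or cannot continue. Section 5.5 puts all available data into the mixed models.

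**The concern.** A dose that has not been taken cannot have caused the reaction under assessment. Yet the reply always includes any such doses, and it goes to members of the team that section 2.6.4 relies on to collect data blind. The protocol does not withdraw a participant after a code break, and it does not move later visits to staff who are still blind.

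What is at stake is the blind of the staff told, at any later drug visit of that participant. Under section 2.11.1, clinicians administer the BPRS and CADSS verbally and a coordinator administers the VAS verbally. All three are secondary outcomes in section 4.2. Advance knowledge of the dose could colour how these are asked and recorded.

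**Working it through.** The protocol states no figure on this point, so there is nothing to reproduce. The check compares what staff know about a future dose under each disclosure rule.

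**Inputs.** Three doses, each given once per participant (section 2.5.1). Random order (section 2.6.1). Planned size 40 participants (section 2.10). Assumption: the 3! = 6 possible orders are equally likely; the protocol says only that the order is random.

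**Chance of correctly naming the dose of a visit not yet given**

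- Blind intact: each dose falls at a given visit in 2 of the 6 orders, so 2/6 = 1/3.
- Only the triggering visit disclosed: 2 of the 6 orders remain possible. They differ in which of the two other doses falls at the future visit, so the chance is 1/2. This holds for a break at visit 1 (for visits 2 and 3) and at visit 2 (for visit 3).
- Visits 1 and 2 both disclosed after an event at visit 2: one order remains, so visit 3 is known by elimination and the chance is 1.
- Full sequence disclosed, as section 2.6.5 now requires: 1.

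| Break at | Later drug visits | Blind intact | Triggering visit only | Current rule |
|---|---|---|---|---|
| Visit 1 | 2 | 1/3 | 1/2 | 1 |
| Visit 2 | 1 | 1/3 | 1/2 | 1 |
| Visit 3 | 0 | – | – | – |

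**Scale.** The plan has 40 × 3 = 120 drug visits. One break at visit 1 exposes at most 2/120 = 1.7% of them, and one at visit 2 at most 1/120 = 0.8%. The protocol gives no expected number of breaks. As an illustration only, three breaks, all at visit 1 and all followed by complete dosing, would expose 6/120 = 5%.

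**Can an exposed visit occur and be analysed?** The allergic-reaction procedure ends the visit and says nothing about later ones. Section 2.11.6 neither promises nor rules out further dosing visits. Any data collected would enter the models under section 5.5. The path is therefore open, though the protocol does not describe it.

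**The case against.** Several stronger readings are tempting, and the protocol does not support them.

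- **That wider disclosure has no safety value.** This goes too far. The triggers in section 2.6.5 are examples, and the section also provides for unblinding outside a visit. Drug visits are 10 to 14 days apart (section 2.5.1), and adverse events may be reported by telephone or correspondence (section 7.1). For a delayed or between-visit event, the relevant visit may not be obvious. A clinician judging whether the participant can continue might also want past or planned doses. What stands is narrower: for assessing a reaction, doses not yet taken add nothing, and the protocol gives no reason for releasing them by default.
- **That every later visit would be run and rated by unblinded staff.** Section 2.6.5 does not say that the whole team is told, or that the participant is. Other blinded staff could run later visits. Further dosing may not follow at all: section 2.11.6 does not mention code breaks, and reduced participation could mean follow-up surveys only. Allergy to MDMA is an exclusion criterion in section 2.9, although the protocol does not say that it is re-applied after enrolment.
- **That the primary result is threatened.** The primary outcome (section 4.1) is FEET activity and connectivity, derived by an image-processing pipeline, with little room for rater bias. Analysts are unblinded by design (section 2.6.4), so this rule adds nothing at that stage.
- **That single-visit disclosure would keep the blind.** It would do so only in part. Each dose occurs once, so one disclosed visit already moves the chance from 1/3 to 1/2. If placebo is disclosed at visit 1, both remaining visits are known to be active drug.

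These objections limit the size of the point. They do not remove it: the rule is explicit, nothing elsewhere narrows it, and it releases more than the named triggers call for.

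**Conclusion.** The point holds as a flaw in a stated rule, of minor severity. After a break at drug visit 1 or 2, the staff told know any remaining dose with certainty. Disclosing only the triggering visit would leave that chance at 1/2. This sits badly with section 2.6.4.

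The loss arises only if the participant has a later drug visit, and it matters only if informed staff take part in that visit. It falls mainly on the BPRS, CADSS and VAS. The overall effect is probably small: at most 2 of 120 planned drug visits per break, with few breaks to be expected. The expectation of few breaks is a judgement, since the protocol gives no rate. The probabilities rest on equally likely orders.

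**What to change.** Amend section 2.6.5 so that the requester gives the study ID and the visit number. The unblinded staff would then release, by default, only the dose of the visit or visits already given that are relevant to the event. Doses not yet given would be released only if the clinician separately requests them for safety. Access to the code when safety requires it is not restricted.

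The cost is a sentence or two of text and no new system, since section 2.6.3 shows that the list is already read by subject ID and visit number. There are two small downsides. Wider disclosure takes one further request. The blind is only partly preserved, and after visit 2 it is not preserved at all if the doses of both earlier visits have to be released.

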### **2.7 Emergency procedure and criteria for discontinuing or modifying allocated interventions**

With input from medical professionals, the following procedures were drafted to address possible emergency scenarios during participant drug sessions:

#### **Myocardial Infarction**

- Administer 162 mg of aspirin (chewable).
- Give sublingual nitroglycerin (0.4mg) unless systolic arterial pressure < 90 mmHg or heart rate is < 50 bpm or > 100 bpm.

#### **Oxygen Desaturation**

Oxygen desaturation is considered a saturation of less than 85%.

- Administer nasal cannula oxygen at 1-6 L/min, titrating to maintain oxygen saturation above 90%.
- If, in 3 minutes, saturation levels do not reach 90%, call 911.

- If participants spontaneously report subjective feelings of air hunger with no evidence of O2 desaturation, they will be given the option of supplemental O2 by nasal cannula.

#### Severe Hypertension

*Severely elevated blood pressure* will be considered a systolic blood pressure > 200 or a diastolic blood pressure > 115 mmHg.

- Attempt non-pharmacologic interventions, such as dimming the lights and creating a relaxing environment.
- Take three consecutive blood pressure measurements, 5 minutes apart, with ECG monitoring. If blood pressure does not decrease after three measurements, the research visit will be discontinued.
- If there is no decrease after the 3rd measurement OR the participant reports chest pain at any time in conjunction with high blood pressure OR has ECG changes suggestive of ischemia in conjunction with high blood pressure, the study clinician will administer NitroStat 0.4 mg sublingual tablet AND call 911.
- If the participant experiences symptoms such as blurred vision, headache, or chest pain in conjunction with severely elevated blood pressure, 911 will be called immediately.

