#### Bradycardia/tachycardia

- Bradycardia is defined as a heart rate < 50 bpm, except in individuals with a known baseline heart rate below this threshold and high exertional capacity. Tachycardia is defined as a heart rate > 150 bpm.
- Three consecutive heart rate measurements will be taken 5 minutes apart, along with an ECG reading. If the heart rate does not start increasing (for bradycardia) or decreasing (for tachycardia) after three measurements, the research visit will be discontinued.
- If the heart rate is < 50 bpm for three consecutive measurements and the participant shows signs of poor perfusion (e.g., altered mental status, signs of shock, chest pain), atropine 0.4mg will be administered AND call 911.
- If the heart rate is > 150 bpm and the participant is stable but the rhythm is irregular on ECG, call 911.
- Determine if a pulse is present:
  - If no pulse (e.g., ventricular tachycardia, ventricular fibrillation, or pulseless electrical activity): Immediately initiate basic life support (BLS) and advanced life support (ACLS) protocol for cardiac arrest (see below).
  - If a pulse is present: Provide oxygen if hypoxic AND call 911 AND insert IV if time while awaiting emergency response.

- Note: We do not have the ability to perform synchronized cardioversion or administer antiarrhythmics.

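### The emergency rules define severe hypertension and abnormal heart rate by a level, but end the visit (and escalate symptom-free hypertension) on an undefined change in direction; the tachycardia 911 instructions also conflict

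*Protocol*

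**What the plan says.** All of the text is in Protocol section 2.7.

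**Severe Hypertension.** The condition is defined as "a systolic blood pressure > 200 or a diastolic blood pressure > 115 mmHg". Three readings are then taken 5 minutes apart with ECG monitoring. On ending the visit: "If blood pressure does not decrease after three measurements, the research visit will be discontinued". On giving nitroglycerin and calling 911, the bullet opens: "If there is no decrease after the 3rd measurement OR the participant reports chest pain at any time in conjunction with high blood pressure". It then adds ischemic ECG changes as a third alternative. A further bullet calls 911 at once if symptoms such as blurred vision, headache or chest pain accompany the severe reading.

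**Bradycardia/tachycardia.** The limits are below 50 bpm (with an exception for some people with a known low baseline) and above 150 bpm. On ending the visit: "If the heart rate does not start increasing (for bradycardia) or decreasing (for tachycardia) after three measurements, the research visit will be discontinued". Three other instructions carry no trend condition:
- atropine plus 911 for a rate below 50 bpm on three readings with poor perfusion;
- "If the heart rate is > 150 bpm and the participant is stable but the rhythm is irregular on ECG, call 911";
- under a pulse check, "If a pulse is present: Provide oxygen if hypoxic AND call 911".

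**Oxygen Desaturation**, for comparison, is tied to a level: "If, in 3 minutes, saturation levels do not reach 90%, call 911".

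**The concern.** Each emergency is entered by crossing a stated limit, but the decision to end the visit does not refer back to that limit. It asks only whether the reading moved in the right direction, and the protocol does not say what counts as movement. For blood pressure it does not say which reading is the reference, how large a fall must be, or whether systolic, diastolic or both must fall, although either alone triggers the rule. The heart-rate sentence is looser still, because the rate need only start to change.

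At stake is whether staff following the text under time pressure would carry on with a participant whose every reading is still in the range that the protocol itself calls severe. The conflicting 911 bullets add a second difficulty: two trained people could read the same page and act differently on a stable, regular rate above 150 bpm.

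**Working it through.** The protocol gives no figure to reproduce, so the check sets the rules side by side and applies them literally to example readings. The readings are assumed; the limits are the protocol's.

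**1. Entry test against the test for each action**

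| Step | Entered on | Decided on |
|---|---|---|
| Hypertension: end visit | systolic > 200 or diastolic > 115 mmHg | no decrease over three readings |
| Hypertension: nitroglycerin + 911 | same | no decrease, or chest pain, or ischemic ECG changes |
| Hypertension: 911 at once | same | symptoms, whatever the trend |
| Heart rate: end visit | < 50 or > 150 bpm | rate has not started to move the right way |
| Bradycardia: atropine + 911 | < 50 bpm | < 50 bpm on three readings plus poor perfusion |
| Tachycardia: 911 | > 150 bpm | stable but irregular rhythm |
| Pulse check: 911 | scope not written | pulse present |
| Oxygen: 911 | saturation < 85% | 90% not reached in 3 minutes |

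Two rows, both for ending the visit, rest on direction alone. The nitroglycerin + 911 row reduces to direction alone once symptoms and ischemic ECG changes are absent.

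**2. Blood pressure, no symptoms, no ischemic ECG changes.** Take systolic 220, 215, 210 mmHg. The fall is 220 − 210 = 10 mmHg, so pressure has decreased. The lowest reading is still 210 − 200 = 10 mmHg above the limit. The visit is not ended and nitroglycerin + 911 is not triggered. Readings of 226, 224, 222 give the same result with a fall of only 4 mmHg. Section 2.7 states no next step for a reading that is falling but still severe.

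**3. The undefined term can also err the other way.** Suppose the trigger reading is 205 and the three that follow are 198, 198, 199. Judged among those three alone there is no decrease, so the visit would end and 911 would be called with every one of them below 200. Judged against 205 there is a decrease. The text does not settle which comparison applies.

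**4. Heart rate.** Take 170, 165, 160 bpm. The rate has started to fall, so the visit is not ended, although 160 > 150. Whether 911 is called depends on the bullets in step 5.

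**5. The two 911 bullets, for a stable, regular rate above 150 bpm with a pulse.**
- The irregular-rhythm bullet does not apply, because the rhythm is regular. By naming irregular rhythm it implies that a stable, regular rate is handled differently.
- The pulse-present sub-bullet applies as written, and calls 911.

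If the second is taken literally, the first is redundant. If the second is meant for a narrower group, that limit is not written.

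**6. How easily chance alone could produce a 'decrease'.** Assume, for illustration only, a constant true level, three exchangeable readings and no ties. There are 3! = 6 equally likely orders.
- The third reading is below the first in 3 of 6 orders = 50%. On that reading of the rule, 'no decrease' fires in 50%.
- At least one successive fall occurs in every order except the strictly rising one: 5 of 6 = 83%. On that reading, 'no decrease' fires in 1/6 = 17%.

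This shows only that the undefined word matters. It is not a rate for real episodes.

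**The case against.** The strongest reply is that a level that opens a procedure and a trend that decides the next step can properly coexist. On that view this is a preference about the form of the rule, and the oxygen rule concerns a different condition. That stands in part: the oxygen rule does not show which form is right for blood pressure. What remains is that 'decrease' is undefined and that the falling-but-still-severe case has no instruction.

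A reader might infer that the rules act only when the reading fails to improve. The text does not support that: chest pain, other symptoms, ischemic ECG changes, poor perfusion with bradycardia and irregular tachycardia all trigger action whatever the trend.

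A reader might also infer that a participant still above 150 bpm can be left without a 911 call. On the literal pulse-present wording, such a participant gets the call, so for tachycardia the trend gap concerns ending the visit, and the 911 question is one of conflicting bullets. That conflict may in turn be a matter of layout, with the pulse check intended as a sub-step for a particular group; if so, the group needs to be written down.

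Finally, a reader might infer that the next check is 30 minutes away. Section 2.5.1 sets routine recording at that interval, but nothing says that monitoring reverts to it after a severe reading. A third reading above the limit still meets the definition of severe hypertension, and section 2.2 gives monitoring and safety assessment to licensed clinicians. The gap is a missing instruction, not an instruction to stand down. Clinical judgment may fill it, though section 2.7 does not provide for that in this case.

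**Conclusion.** The concern holds in a limited form. Two visit-discontinuation rules (blood pressure and heart rate), and one escalation step (nitroglycerin + 911 for severe hypertension without symptoms or ischemic ECG changes), depend on an undefined change in direction and not on the limits that define the emergency. Followed literally, they do not fire for a participant whose three readings improve slightly but all remain past the limit, and nothing is stated for that participant. The 911 wording for a stable, regular rate above 150 bpm with a pulse is inconsistent.

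This rests on a literal reading of section 2.7 and needs no outside clinical standard. How often it would occur cannot be estimated from the protocol. The 17% and 50% in the working depend on an assumed constant level with exchangeable noise; a rising pressure, for example, would make 'no decrease' fire more often. They should not be quoted as the share of episodes missed. The defect is nevertheless worth correcting because it sits in the written cardiovascular emergency steps and is cheap to repair.

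**What to change.** The clinical team should make three changes to section 2.7:

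1. Under Severe Hypertension and under Bradycardia/tachycardia, reconcile the discontinuation and escalation wording with the limits those subsections define, so that staff can tell what counts as a change, against which reading, and how it relates to the limit. For blood pressure, say whether this means systolic, diastolic or both.
2. State what happens when a reading is improving but still past the limit.
3. Reconcile the irregular-rhythm bullet and the pulse-present sub-bullet into one 911 instruction, and state whom the pulse check covers.

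The form of the rule and every threshold are for the study clinicians; none is proposed here. The cost is protocol rewording and staff retraining, and possibly a few more visits discontinued or escalated.
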